**Fig. 2 Fig2:**
[figure not shown]
PETNECK2 randomised controlled trial schema. Schema for the PETNECK2 randomised controlled trial to assess the efficacy and cost-effectiveness of patient-initiated active surveillance compared to the routine clinical follow-up. * 6-to-14 months post-treatment is permitted for registration into the RCT. Randomisation must occur 11–14 months post-treatment. HNC, head and neck cancer; I&S, information and support; PROM, patient-reported outcome measures; RCT, randomised controlled trial

Randomisation of 698 patients is performed electronically with a 1:1 allocation ratio and remotely by recruiting centres, using a computer minimisation program incorporating a random element developed by the Cancer Research UK Clinical Trials Unit (CRCTU), Birmingham, UK. Stratification variables are: centre; HPV status/tumour site combination; tumour stage; and baseline FCR score.

Recruitment will be over 33 months, with participants followed up for at least 12 months from randomisation, incorporating follow-up using electronic medical records.

A list of the PETNECK2 centres can be requested from the PETNECK2 Trial Office ([contact]). The Standard Protocol Items: Recommendations for Intervention Trials (SPIRIT) checklist is provided as Additional File 1 [39]. The World Health Organization (WHO) Trial Registration Data Set is provided in Additional File 2.

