#### Fear of cancer recurrence

A nine-item FCR Inventory-Short form [47] regarding “fear, worry, or concern about cancer returning or progressing” [19] is being used during PETNECK2. This is given to all patients at baseline (11–14 months post-treatment) and at approximately 12- and 24-months post-randomisation for those patients enrolled in the RCT.

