Qualitative data from both arms of RCT will be analysed at two time points using thematic analysis [50]. This analytical method was selected as it is a flexible approach and considers both inductive and deductive approaches employing a Leventhal’s self-regulation model to guide us as a theoretical lens [51]. The self-regulation model will help understand the patients’ illness perceptions/beliefs, symptom appraisal, and how they interact with emotional experiences such as fears about cancer recurrence. We will employ this model to guide our analyses inductively. The thematic analyses will be conducted in six phases: phases one and two: familiarisation and coding; phase three: theme development; phases four and five: reviewing and refining themes; phase six: producing the report. We will aim to explore if there are any qualitative differences in the way that the intervention helps or hinders with fears of cancer recurrence and how these fears change or do not change over time.

The overall FCR score will be analysed as a continuous outcome with summary data presented to summarise scores at the baseline and 12-month timepoints. A t-test of the change from baseline to 12 months will be assessed to determine any difference between the two arms. Linear regression will also be employed to model FCR score and adjust for any important factors.

The symptom and function scores will be calculated for each of the EORTC questionnaires returned and presented graphically and compared across the assessment time points. The overall global score from the EORTC questionnaires and the EQ-5D-5L score (and thermometer) will be compared between arms and analysed using longitudinal methods with consideration being given to missing data. Differences in all measures (overall, function and symptom) will be evaluated over time using appropriate regression analysis adjusting for baseline domain scores and other key factors where applicable. EQ-5D-5L and survival will be combined to determine QALYs for the health economic analysis.

For the patients on the intervention arm, the individual self-efficacy and motivation questions will be summarised at the evaluated timepoints and also used to determine composite scores for: (i) self-efficacy and confidence; (ii) personal motivation; and (iii) external motivation factors. These will also be correlated with intervention resource usage.

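### The named between-arm test of fear of cancer recurrence is an unadjusted change-score t-test, although baseline FCR is a minimisation factor; the adjusted regression should lead

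*Protocol article*

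**What the plan says.** In the Protocol article, the Statistical analysis plan section treats the FCR score as continuous, with "summary data presented to summarise scores at the baseline and 12-month timepoints". It then names the comparison: "A t-test of the change from baseline to 12 months will be assessed to determine any difference between the two arms". The next sentence reads: "Linear regression will also be employed to model FCR score and adjust for any important factors". It does not name the factors or the time point, and it does not say which of the two analyses carries the conclusion.

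Three other places bear on this choice:

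- The Randomised controlled trial (RCT) section says patients are allocated "using a computer minimisation program incorporating a random element". It continues: "Stratification variables are: centre; HPV status/tumour site combination; tumour stage; and baseline FCR score".
- The Fear of cancer recurrence section and Table 2 schedule the questionnaire at baseline "and at approximately 12- and 24-months post-randomisation for those patients enrolled in the RCT".
- The Statistical analysis plan section handles the other patient-reported scores differently. The global EORTC and EQ-5D-5L scores are to be "analysed using longitudinal methods with consideration being given to missing data", and the regressions for those measures adjust for each domain's baseline value. The Cox model for overall survival is stratified for the stratification factors.

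**The concern.** The article makes a positive choice of test here, and on its own terms the choice is hard to defend. FCR is the only patient-reported score used in the allocation, yet its named test takes no account of that and adjusts for nothing. A change score does use the baseline, but it fixes the slope on baseline at 1 when the efficient slope is rho. After allocation balanced on baseline FCR, the ordinary t-test also estimates its standard error as if that balance had been left to chance.

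The consequence is wider intervals and a lower chance of seeing a real difference than the data allow. The Background states that no study has examined how follow-up regimens affect FCR, and the trial has a nested study on it, so an imprecise answer would be a pity. Two 12-month analyses with no stated lead, one with open covariates, also leave room to choose between answers.

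**Working it through.** **The plan's own figures.** The article gives no standard deviation, target difference, correlation or power for FCR, so there is no FCR figure to reproduce. Its 90 events and 698 patients belong to overall survival and do not bear on this point. Rho, the effect size and the number of responders below are all assumptions.

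**Step 1: relative precision.** Take equal variances at baseline and 12 months, in units of the score variance. The variance per patient is 2(1 − rho) for the change score and 1 − rho² for the baseline-adjusted analysis (ANCOVA). The ratio is (1 − rho²) / [2(1 − rho)] = (1 + rho)/2. The extra patients the t-test needs for equal precision are 2/(1 + rho) − 1.

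| rho (assumed) | Change score | ANCOVA | Ratio | Extra patients for t-test |
|---|---|---|---|---|
| 0.3 | 1.40 | 0.91 | 0.65 | 54% |
| 0.5 | 1.00 | 0.75 | 0.75 | 33% |
| 0.6 | 0.80 | 0.64 | 0.80 | 25% |
| 0.7 | 0.60 | 0.51 | 0.85 | 18% |
| 0.8 | 0.40 | 0.36 | 0.90 | 11% |

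The ratio is below 1 for every rho below 1, so the direction does not depend on the assumed value.

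**Step 2: power if baseline balance is left to chance.** Assume 300 responders per arm, a true difference of 0.2 SD and a two-sided 5% test. Power = Φ(0.2/√(2V/300) − 1.96), where V is the variance from step 1.

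- rho 0.5: t-test Φ(0.2/0.0816 − 1.96) = 68.8%; ANCOVA Φ(0.2/0.0707 − 1.96) = 80.7%.
- rho 0.6: t-test Φ(0.2/0.0730 − 1.96) = 78.2%; ANCOVA Φ(0.2/0.0653 − 1.96) = 86.5%.
- rho 0.7: t-test Φ(0.2/0.0632 − 1.96) = 88.5%; ANCOVA Φ(0.2/0.0583 − 1.96) = 92.9%.

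**Step 3: power under perfect baseline balance.** Minimisation on baseline FCR moves the trial away from step 2. In the limit of exact balance, the change-score and ANCOVA estimates coincide, so the estimate varies with the ANCOVA standard error while the t-test still judges it against the larger one. T-test power becomes Φ((0.2 − 1.96 × SE of change) / SE of ANCOVA).

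- rho 0.5: Φ((0.2 − 1.96 × 0.0816)/0.0707) = 71.4%, against 80.7% for ANCOVA.
- rho 0.6: 80.8%, against 86.5%.
- rho 0.7: 90.4%, against 92.9%.

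The gaps fall from about 12, 8 and 4 points in step 2 to about 9, 6 and 3. In this limit the whole gap comes from the overstated standard error. Minimisation with a random element lies between the two cases.

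**Step 4: type I error.** A simulation used 698 patients, with allocation balanced within a two-level split of baseline FCR and 40% above the cut (split and cut are assumptions). The t-test rejected a true null in about 3.1% of runs at rho 0.4 and 3.4% at rho 0.6, against a nominal 5%. ANCOVA gave about 5.2% and 4.9%. Under allocation that ignored baseline, the t-test gave about 5.4% and 4.9%. Balancing on baseline is therefore what makes the unadjusted test conservative.

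**Step 5: the 24-month visit.** Recruitment runs 33 months with at least 12 months of follow-up. With uniform accrual and closure 12 months after the last entry (both assumed), a patient entering at month t has 45 − t months available. Reaching 24 months needs t ≤ 21, that is 21/33 = 64% of patients before death or non-response. The visit is incomplete by design but still substantial.

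**The case against.** The strongest reply is that an adjusted analysis is already planned. Baseline FCR is an obvious candidate for an important factor, and if the regression includes it, that analysis loses nothing. This stands. A reader might infer from the t-test sentence that FCR will be compared only without adjustment, or that the trial throws away 15% to 25% of its FCR information. The documents do not support either reading, because the variance loss belongs to the t-test alone.

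A second reply is that covariate lists and the ranking of analyses for a secondary outcome are commonly left to a separate statistical analysis plan. That is fair, and the unnamed covariates would not by themselves be a finding. The t-test is different: the article states it, and attaches to it the task of determining the difference between arms.

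Third, a reader might suspect that ignoring the minimisation factors produces false positives or bias. It does not. The change-score estimate is unbiased under the allocation used, and step 4 shows the error rate falling below nominal.

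Fourth, 12 months is the FCR visit that minimum follow-up covers for every patient, so testing there is defensible. A reader might infer that the 24-month data will be discarded. The regression sentence is not limited to 12 months, so the text shows only that no 24-month FCR analysis is stated.

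**Conclusion.** The point holds as a modest, worthwhile correction. The article names a between-arm FCR test that is less precise than a baseline-adjusted model for any rho below 1 and, after minimisation on baseline FCR, has a standard error that is too large. The adjusted alternative beside it neither commits to baseline FCR nor is said to lead.

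The nominal variance ratio is 0.75 to 0.85 for rho 0.5 to 0.7. Under the assumptions of 300 responders per arm and 0.2 SD, the power shortfall is about 9 to 12 points at rho 0.5, 6 to 8 at rho 0.6 and 3 to 4 at rho 0.7. The smaller figure in each pair applies as baseline balance becomes exact. None of these inputs is in the article. The cost is lost precision and a conservative test on a secondary outcome, with no effect on the survival analysis. The missing 24-month FCR analysis is a supporting point only.

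**What to change.** Name the already planned linear regression as the lead between-arm FCR analysis at 12 months, with baseline FCR as a continuous covariate and the other minimisation factors (centre, HPV status/tumour site, tumour stage) included. Report the adjusted difference with its confidence interval. Drop the t-test, or label it supportive.

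The 24-month scores can be added as a secondary contrast, for example in a repeated-measures model covering both visits, with a statement that they may be incomplete because minimum follow-up is 12 months. The form of that model is a matter of preference; the baseline-adjusted lead analysis is the necessary change.

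The cost is a change of wording before the data are analysed. All the variables are already collected, and neither the sample size nor patient contact changes.

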#### Control arm of randomised controlled trial

Standard of care clinical follow-up as per UK HNC guidelines is followed at the discretion of the participating centre, e.g. two-monthly in the second year after the end of treatment, and three-to-six monthly in years three-to-five.

The schedule of events for patients in either the PETNECK2 feasibility study and RCT have been included in Tables 1 and 2, respectively.

**Table 1 Tab1:** PETNECK2 feasibility study patient pathway

Assessments	6–14 months post- treatment	Baseline 11–14 months post-treatment	Post PET-CT scan	Follow-up appointment (1–2 months post education session)	Open urgent appointment^a^
Informed consent	x				
Registration	x				
Quality of Life & Resource Use Questionnaires^b^		x		x	
PET-CT scan^c^		x			
PET-CT consultation			x		
PETNECK2 Education Session			x		
Qualitative interview				x	
Clinical Interaction for Symptom Assessment and evaluation					x

^**a**^Multiple and at any time point after the education session for the duration of the feasibility study

^b^To include EQ-5D-5L, EORTC QLQ-C30 and H&N43, Fear of Cancer Recurrence

^c^If recurrent disease diagnosed on PET-CT and confirmed on further investigation, no further study intervention will be undertaken. Follow-up data will still be collected

**Table 2 Tab2:** PETNECK2 randomised controlled trial patient pathway

Assessments	6–14 months post-treatment	Baseline 11–14 months post- treatment	Post PET-CT scan	Open urgent appointment^d^	6 months* follow-up	12 months* follow-up	24 months* follow-up
Informed consent	x						
Registration	x						
Randomisation		x					
Fear of Cancer Recurrence (FCR) questionnaire		x				x	x
EORTC questionnaires (QLQ-C30 and QLQ-H&N43)		x				x	x
EQ-5D-5L & Resource Use questionnaires		x			x	x	x
Self-efficacy & motivation questionnaire		x			x	x	
CQC question					x	x	x
Blood, oral rinse, and tissue collection^b^		x				x	
Fear of Cancer Recurrence interview^c^		x				x	
PET-CT scan^a^		x					
PET-CT consultation^a^			x				
PETNECK2 Education Session^a^			x				
Clinical interaction for sympton assessment and evaluation				x			

^a^Patients randomised to intervention arm only

^b^Optional - patients consenting to PETNECK2 Collect sub-study

^c^Optional - a subset of patients with clinically significant FCR (taken from baseline FCR questionnaire with cut-off ≥ 22) consenting to FCR interviews. The first of these should take place before the PET-CT scan

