#### Self-efficacy and motivation

Patients are asked to answer a set of questions about their self-checking habits. At baseline this ascertains whether they self-check or not, while at 6- and 12-months, it will assess the frequency of their self-checking. Patients are also requested to indicate their confidence levels to know what is normal for them/notice any changes or new symptoms, manage to check monthly for changes, and be able to report when they have noticed a change. This is based on published guidelines for constructing self-efficacy scales [44]. Patients are also asked to complete a modified version of the Treatment Self-Regulation Questionnaire to assess reasons for engaging in patient-initiated follow-up [45]. All patients are asked to complete these questionnaires at baseline, 6- and 12-months post-randomisation. At 6- and 12-months, two items from the Autonomy and Competence in Technology Adoption Questionnaire (ACTA) [46] are also employed to assess the extent to which intervention arm patients perceive that they are competent to use the App/booklet. The self-checking, self-efficacy and motivation questions are included as part of the Questionnaire Pack.

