#### Randomised controlled trial

The primary outcome measure is overall survival time defined as the interval between the date of randomisation and the date of death from any cause. Patients who have not died at the time of analysis will be censored at the date when they were last known to be alive. Follow up for survival will be collected on trial Case Report Forms (CRFs), by linking with NHS Digital and other health registries and annual hospital record checks.

Secondary outcome measures include:

Cost-effectiveness as measured by incremental cost per quality-adjusted life year (QALY) gained (combining EQ-5D-5L utility scores with overall survival data), and resource use data collection, including number and reasons for healthcare visits.Recurrence and distant metastasis encompassed by:
Disease free survival time defined as the interval between the date of randomisation and the date of a contributing event (either a recurrence (to include local, regional, and distant) or death from any cause and excluding any new primary cancer). Patients who are alive and disease-free at the time of analysis will be censored at the date when they were last known to be alive and disease-free.Time from treatment to first detection of recurrence defined as the interval between the completion of the patient’s definitive preliminary treatment (not including any neck dissection that might have been implemented at three months) and a recurrence of any nature (local, regional, or distant). Patients who die before a recurrence will be censored at their date of death.Details of recurrences, including location (specific details on site and whether local, regional, or distant), TNM stage at detection of recurrence and subsequent treatment for recurrence.
Quality of life assessed by the EORTC-QLQ-C30, EORTC QLQ-H&N43, and EQ-5D-5L questionnaires.Fear of cancer recurrence assessed quantitively by the FCR questionnaire and qualitatively by patient interviews.Patient experience measured by the CQC patient experience question.Patient self-efficacy and motivation will be assessed using responses from the individual self-efficacy and motivation questions.Time to receiving an urgent review appointment, as well as the number and timings of appointments requested (for patients in the intervention arm only).

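### Self-efficacy and motivation are collected in both arms as a secondary outcome, but the only stated analysis is of the intervention arm, so no randomised comparison is planned

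*Protocol article*

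**What the plan says.** Collection covers both arms. On the self-checking, self-efficacy and motivation questions, the section Self-efficacy and motivation states: "All patients are asked to complete these questionnaires at baseline, 6- and 12-months post-randomisation". Table 2 (RCT patient pathway) agrees. Its row "Self-efficacy & motivation questionnaire" is marked at baseline, 6 and 12 months and does not carry the footnote "a^Patients randomised to intervention arm only", which is attached to the PET-CT scan, the PET-CT consultation and the education session. One component does belong to a single arm: two technology-competence (ACTA) items at 6 and 12 months "are also employed to assess the extent to which intervention arm patients perceive that they are competent to use the App/booklet".

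The RCT outcome list under Trial outcomes includes the measure as a secondary outcome with no arm restriction: "Patient self-efficacy and motivation will be assessed using responses from the individual self-efficacy and motivation questions". The next item in that list, on urgent appointments, is expressly confined to the intervention arm.

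The Statistical analysis plan section gives one analysis of this outcome: "For the patients on the intervention arm, the individual self-efficacy and motivation questions will be summarised at the evaluated timepoints". The same answers are used to build three composites (self-efficacy and confidence, personal motivation, external motivation), and then: "These will also be correlated with intervention resource usage".

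**The concern.** The new follow-up model depends on patients monitoring themselves and making contact when something changes. The Discussion names barriers to help-seeking as an area of risk. The questionnaire measures this step directly: whether and how often patients self-check, and how confident they are that they would notice and report a change. Whether the education session and resource improved these is a question that randomisation can answer, and the control answers needed for it are being collected.

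If the analysis follows the published wording, control patients complete the questionnaires at three time points for no stated purpose. A reader of the results would see intervention-arm scores with nothing to set them against. Any movement in those scores could reflect time since treatment or repeated questioning as much as the intervention. A between-arm result would also help in interpreting the survival finding, whichever way it falls.

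**Working it through.** The plan gives no figure for this outcome, so the main check sets the sections side by side.

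- **Who answers:** all patients, at baseline, 6 and 12 months (Self-efficacy and motivation; Table 2).
- **Status:** RCT secondary outcome, no arm restriction (Trial outcomes).
- **Analysis:** summaries, composites and a resource-usage correlation, introduced as being for intervention-arm patients (Statistical analysis plan).
- **Other outcomes in the same section:** the change in fear-of-recurrence score is tested between arms. The EORTC global score, EQ-5D-5L, further treatment after recurrence and follow-up visit counts are compared between arms. Recurrence details, which are only descriptive, are still tabulated by arm.

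Among the patient-reported scales answered by all patients, the stated analysis of this one alone names a single arm.

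**Would a comparison be informative?** This part is for scale only. The article gives 698 patients randomised 1:1, so 698/2 = 349 per arm. It gives no return rate at follow-up and no correlation between baseline and follow-up, so both are assumed below. The nearest figure is the internal pilot target of more than 75% completion of baseline patient-reported outcomes. Tests are two-sided at 5%.

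*With baseline adjustment (85% return, correlation 0.5):*
- Patients per arm: 0.85 × 349 ≈ 297.
- SE of the adjusted difference: √[2 × (1 − 0.5²)/297] = √(1.5/297) = 0.071 SD.
- Detectable difference at 80% power: 2.80 × 0.071 ≈ 0.20 SD.

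*Without baseline adjustment (75% return):*
- Patients per arm: 0.75 × 349 ≈ 262.
- SE of the difference: √(2/262) = 0.0874 SD.
- At 80% power: 2.80 × 0.0874 ≈ 0.245 SD.
- At 85% power (1.96 + 1.04 = 3.00): 3.00 × 0.0874 ≈ 0.26 SD.

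Across these assumptions the trial could detect a difference of roughly 0.20 to 0.26 SD in the self-efficacy/confidence composite.

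**The case against.** Several points on the other side have force.

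- **The analysis sentence does not say that it is exclusive.** Elsewhere the authors write the restriction out when they mean it. A reader might infer that the control data will be discarded, but the article supports only that no use is stated for them. The full protocol and the SAP are not shown and could add a comparison. Even so, the article is not silent: it states an analysis and names one arm, so a SAP that followed it would contain no contrast.
- **No comparison is promised.** The outcome list says the measure will be assessed, not compared, and a secondary outcome may be descriptive. This is true, but a descriptive outcome collected in both arms would ordinarily be shown for both, as recurrence details are.
- **No before-after claim is made.** A reader might conclude that the plan intends to infer an effect from change within one arm, exposed to regression to the mean. The text does not support that. It proposes summaries at each time point and a correlation, and that correlation makes sense only in patients given the resource.
- **The motivation items may not transfer.** The modified Treatment Self-Regulation Questionnaire asks why patients engage in patient-initiated follow-up, whereas controls have scheduled visits. This stands, and it limits the remedy.
- **Other evidence on behaviour exists.** Visit counts are compared between arms, and requested appointments are summarised with timing and reasons. It would therefore be too strong to say that the trial can learn nothing about whether patients acted. The intervention also includes a PET-CT scan, so a difference in self-efficacy could not by itself explain a survival result.

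**Conclusion.** The point holds as a mismatch between collection, outcome list and analysis. Following the text, up to 349 of 698 patients supply data with no stated use, and the trial has no randomised estimate of the effect on self-checking or on confidence to notice and report symptoms. The case is clear for those two measures and weaker for the motivation composites, whose meaning in controls is doubtful.

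The feasibility range of 0.20 to 0.26 SD rests on assumed return of 75% to 85% and an assumed baseline correlation of 0 to 0.5. It shows that a comparison is worth making; it does not measure any harm. The primary outcome, the sample size and the non-inferiority conclusion are untouched, so this is a worthwhile correction to a secondary analysis and no more than that.

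**What to change.** In the Statistical analysis plan section:

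1. Add a between-arm comparison of the self-efficacy/confidence composite at 6 and 12 months, by ANCOVA or a mixed model adjusted for the baseline composite and the minimisation factors.
2. Add a between-arm comparison of self-checking frequency at 6 and 12 months, adjusted for the baseline item on whether the patient self-checks.
3. Tabulate the personal and external motivation composites by arm, descriptively, and note that their items concern patient-initiated follow-up and may not be comparable in controls.
4. Keep the ACTA items and the correlation with resource usage as intervention-arm analyses, and say so.

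If the sponsor intends a one-arm description after all, the outcome list should say this and the reason for questioning controls should be given.

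The cost is a few lines of analysis wording and a small amount of extra secondary analysis. No new data, visits or patients are needed.
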